# Modafinil In Debilitating fatigue After Stroke (MIDAS): study protocol for a randomised, double-blinded, placebo-controlled, crossover trial

**DOI:** 10.1186/s13063-016-1537-4

**Published:** 2016-08-17

**Keywords:** Fatigue, Ischaemic stroke, Stroke recovery

## Abstract

**Background:**

Fatigue is a common symptom in stroke survivors for which there is currently no proven therapy. Modafinil is a wakefulness-promoting agent with established benefits in other disease models. We aim to test if modafinil will improve patient’s self-reported fatigue scores when compared to placebo and if therapy results in increased quality of life.

**Methods/design:**

MIDAS is a phase II, single-centre, prospective, double-blinded, randomised, crossover trial of modafinil for the treatment of persistent fatigue in survivors of ischaemic stroke. The inclusion criteria will require an average score of 12 or more across all domains of the Multi-dimensional Fatigue Inventory (MFI-20) and the diagnosis of a stroke more than 6 months prior. Patients will be randomised 1:1 to receive either modafinil 200 mg daily or placebo for a period of 6 weeks, after which a crossover will occur where patients who are on modafinil will begin taking placebo and vice versa. The primary outcome will be improvement in fatigue as measured by the MFI-20. Secondary outcomes will include changes in the Fatigue Severity Scale, improved cognition measured using the Montreal Cognitive Assessment, improvement in mood as determined by the Depression, Anxiety and Stress Scale and improvement in each patient’s stroke-specific quality of life score. All participants will also undergo magnetic resonance imaging (MRI) at baseline, crossover and study conclusion to measure cerebral blood flow on arterial spin labelling and brain activity on resting state functional MRI. This study will comply with the CONSORT guidelines. The projected sample size requirement is 36 participants in a crossover trial giving a power of 80 % and a type-1 error rate of 0.05.

**Discussion:**

MIDAS seeks to enhance the quality of life in stroke survivors by assisting or resolving stroke-associated fatigue.

**Trial registration:**

ACTRN12615000350527, registered on the 17 April 2015.

Protocol version 3, approved 16 June 2015.

**Electronic supplementary material:**

The online version of this article (doi:10.1186/s13063-016-1537-4) contains supplementary material, which is available to authorized users.

## Background

Severe fatigue is reported in approximately half of all stroke survivors [1, 2] and can persist for years after the index event, resulting in a reduction in quality of life. Fatigue is a common symptom in chronic disease and is hypothesised to be caused by a combination of organic brain lesions and psychosocial stress related to lifestyle adjustment. Fatigue can also be caused by sleep apnoea [3] and is a pivotal component of depression [4], which is also common after stroke. Fatigue after stroke has been identified to be an independent predictor of poor outcome [5]; whether this is due to the severity of the stroke itself or to fatigue directly contributing to poor outcome is not yet understood. However, neuroimaging studies have found no clear association between characteristics of the brain lesion (e.g. location, pathological type) and fatigue [6]. Currently there are no proven therapies for post-stroke fatigue. In the present study, we seek to investigate if 200 mg daily of modafinil can improve post-stroke fatigue and other aspects of quality of life in a community-dwelling population.

Modafinil is a nonamphetamine wakefulness-promoting agent with limited side effects that is currently used to treat excessive sleepiness associated with narcolepsy, shift-work sleep disorder and obstructive sleep apnoea. Modafinil has also been used in the treatment of fatigue associated with Parkinson’s disease, multiple sclerosis, traumatic brain injury and post-polio syndrome [7]. Several case reports advocating the use of modafinil in stroke patients have been published [8, 9]. However, a recent study of modafinil treatment immediately after stroke was negative due to resolution of fatigue in both the control and therapy groups [10]. We hypothesised that treatment with modafinil would reduce the severity of self-reported fatigue in stroke survivors compared to placebo.

## Methods/design

Modafinil In Debilitating fatigue After Stroke (MIDAS) will be a phase II, single-centre, prospective, double-blinded, randomised, crossover trial to investigate if modafinil reduces the burden of fatigue after ischaemia in patients who report ongoing severe fatigue (as measured by the Multidimensional Fatigue Inventory (MFI-20)). This study will apply the Consolidated Standards of Reporting Trials (CONSORT) and the Standard Protocol Items: Recommendations for Interventional Trials (SPIRIT) (Additional file 1: Figure S1) [11] guidelines. The project protocol was developed by researchers from the University of Newcastle without external influence. Data management includes assigning participants unique study identifiers and scanning participant documents and backup on secured computers as detailed in the protocol. The projected total sample size requirement is 36 participants. Ethical approval was granted by the Hunter New England Human Research Ethics Committee in accordance with the Helsinki Deceleration on 9 June 2015, reference 15/04/15/3.02. Because this is a single-centre study of 36 participants, no Data Safety Monitoring Board will be required.

### Patient population

Patients will be recruited following from the Newcastle, NSW, Australia community and from stroke clinics at John Hunter Hospital. Inclusion criteria will be patients aged over 18 years with a history of stroke at least 6 months previously and an average score of 12 across each domain of the MFI-20. All participants are required to provide informed consent.

Inclusion criteria:Being 18 years of age or olderHaving suffered a stroke or transient ischaemic attack (TIA) at least 3 months previousHaving persistent self-reported fatigue with a MFI-20 score of 12 or moreA modified Rankin Score (mRS) of 3 or lessAble to speak reasonable English, understand instructions and be able to complete tests and questionnaires on their own or with minimal supportAble to give informed consent

Exclusion criteria:Having pre-existing depression, dementia or other neuropsychiatric diseaseHaving other diagnoses with fatigue as a known symptom, e.g. chronic fatigue syndrome, multiple sclerosisHaving stroke induced by trauma, infection or surgeryCurrent or past drug abuseKnown contraindication to treatment with modafinilKnown active malignancy, any intracranial tumor, subdural or epidural hematomaKnown contraindications to MRI scanning, e.g. claustrophobia, cardiac pacemaker or other implantsKnown cause of fatigue (i.e. sleep apnoea)Having renal or hepatic impairmentUse of benzodiazepines or antiepileptic drugsPatients on immunosuppression or known immunodeficiency state, e.g. HIV

Study drug will be discontinued if there are any adverse events due to the drug (i.e. rash).

### Therapy

Participants will be randomised 1:1 to modafinil 200 mg per day or placebo. All participants will be provided with 6 weeks’ worth of study drug after randomisation. After 6 weeks, participants will be asked to return to the study centre for assessments and to return study drug bottles to assess compliance. After the study drug has been returned, participants will have a 1-week washout period. Once the washout period has been completed, participants will again be asked to return to the study centre and crossover will occur where participants who initially received modafinil will be given a placebo or those who were given placebo will receive modafinil. Lastly, after 6 weeks on the second round of the study drug, participants will be asked to return to the study centre for assessments and to return study drug bottles to assess compliance.

### Assessments

Assessments will be carried out at baseline, in the last week of the first 6-week treatment arm, after a 1-week washout period and in the last week of the second 6-week treatment arm (Fig. 1). The assessment at each time point will include the MFI-20, the Montreal Cognitive Assessment (MoCA), the Fatigue Severity Scale (FSS), the Depression, Anxiety and Stress Scale (DASS 42) and the Stroke-specific Quality of Life (SSQoL) scale. All assessments will be carried out by research staff blinded to treatment. All participants will also complete magnetic resonance imaging (MRI) sessions at baseline, crossover and study conclusion to measure cerebral blood flow on arterial spin labelling (ASL) and brain activity on resting state functional MRI (rsfMRI). Drug adherence will be monitored through tablet return for each patient in each strata (placebo or active drug).

**Fig. 1 Fig1:**
[figure not shown]
Standard Protocol Items: Recommendations for Interventional Trials (SPIRIT) diagram for the MIDAS trial. A SPIRIT diagram of the study procedures. Following enrolment, patients are randomised to either active drug or placebo. Following 6 weeks of therapy and a 1-week washout, patients are crossed over either to active drug or placebo. All patient assessments are carried out at the start and conclusion of each therapy round. MRI scans are performed at the start of the study and at the end of each therapy round. *DASS 42,* Depression, Anxiety and Stress Scale, *FSS,* Fatigue Severity Scale, *MFI,* Multidimensional Fatigue Inventory, *MoCA,* Montreal Cognitive Assessment, *MRI* magnetic resonance imaging, *SSQoL,* Stroke-associated Quality of Life

### Consent and randomisation

Participant consent will be obtained following screening with the MFI-20 by an independent researcher who is not involved with the routine care of the participant. Participants will be referred to the research team by clinicians who see stroke survivors in clinics. Where appropriate the clinician will introduce the study to potential participants if the clinician believes that the potential participant will meet the inclusion criteria and be willing and able to provide informed consent as well as maintain study enrolment for the full length of the trial.

Patients will be randomly allocated to taking either 200 mg modafinil or an identical placebo daily. Treatment allocation will be performed by the local pharmacy according to a randomisation schedule generated by an independent statistical support unit (Clinical Research Design, IT, and Statistical Support, CReDITSS) at the Hunter Medical Research Institute. Randomisation will be based on a computer-generated list of random numbers with varying block size, linked to a unique treatment number. All study participants and researchers outside of the pharmacy will be blinded to treatment allocation. Unblinding will occur in the event of an adverse or serious adverse event and will be performed by the pharmacy at the request of the study researchers or clinicians. A serious adverse events related to modafinil therapy can include developing a rash, or any event causing study participant withdrawal or hospitalisation while in the study. An adverse event will be defined as the occurrence of headache, nausea, anxiety/nervousness, insomnia, and diarrhoea.

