### Primary outcomes

The primary outcome will be a significant reduction in the self-reported MFI-20 score during modafinil treatment compared to that participant’s difference during the placebo period.

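### The unblinding provision covers any adverse event, and adverse events are defined as common minor complaints, which contradicts the protocol's own blinding commitments

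*Protocol article*

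**What the plan says.** The provision and the definition stand together in the protocol article under Consent and randomisation. The provision reads "Unblinding will occur in the event of an adverse or serious adverse event and will be performed by the pharmacy", and the sentence goes on to say that this is "performed by the pharmacy at the request of the study researchers or clinicians". The definition follows: "An adverse event will be defined as the occurrence of headache, nausea, anxiety/nervousness, insomnia, and diarrhoea". Neither sentence sets a threshold of severity, a link to study drug, or a need to know the allocation. Serious events are described separately (rash, or an event leading to withdrawal or admission), so the wider category was included in the provision by name.

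Three other statements bear on it:

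- The same section promises that "All study participants and researchers outside of the pharmacy will be blinded to treatment allocation".
- Assessments states that "All assessments will be carried out by research staff blinded to treatment".
- Patient population ties discontinuation of study drug to events attributed to the drug, a narrower condition than the one that opens the code.

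The primary outcome is a "significant reduction in the self-reported MFI-20 score during modafinil treatment compared to that participant’s difference during the placebo period". Under Therapy, the second period is always the opposite of the first: "participants who initially received modafinil will be given a placebo or those who were given placebo will receive modafinil".

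**The concern.** A double-blind trial with a patient-reported primary outcome depends on the participant, and whoever administers the questionnaires, not knowing the current treatment. The listed complaints are common and can occur on either treatment. Read literally, one headache is enough for the code to be opened. Those who may ask for it include researchers whom the same section says are to stay blinded.

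The crossover raises the stakes. In a parallel-group trial a code break reveals one allocation. Here it reveals the whole sequence, so a break early in the trial can reach every later score from that participant. If the listed complaints are more frequent on one treatment, loss of the blind is also related to treatment, and recruiting more participants would not remove the resulting bias.

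**Working it through.** **1. The statements side by side.**

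| Element | What the protocol fixes | Condition attached |
|---|---|---|
| Trigger for unblinding | any adverse event, serious or not | none on severity, causality or need |
| Adverse event | any of five listed non-serious complaints | none |
| Who may ask | study researchers or clinicians | no criterion for asking |
| Who stays blinded | participants and all non-pharmacy researchers | unqualified |
| Who assesses | blinded research staff | unqualified |
| Discontinuation of study drug | events attributed to the drug | causality |

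The first three rows cannot operate as written while the fourth stays true. A researcher who obtains the code is a researcher outside the pharmacy who is no longer blinded. The fifth row stays true only if code recipients and assessors are kept apart, which the article does not say.

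**2. Which scores a code break can reach.** The MFI-20 is recorded at baseline, in the last week of period 1, after the 1-week washout, and in the last week of period 2.

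- Break before the period 1 assessment: the end-of-period-1, post-washout and end-of-period-2 scores are all exposed.
- Break after the period 1 assessment but before period 2 starts: the end-of-period-2 score is exposed, and the post-washout score too if it has not yet been taken.
- Break in period 2: only the end-of-period-2 score is exposed. The period 1 scores were already collected blind.

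**3. How many participants could meet the trigger.** The protocol's only design figure is the sample size, 34 required and 36 to be recruited. It reproduces if SD 14 is per period with zero within-participant correlation. The SD of the difference is then 14 × √2 = 19.8, and a two-sided 5% t-test for a 10-point difference at 80% power needs 33, or 34 with equal sequences. The figure is not in dispute here; only the 36 is used below.

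The protocol gives no event rate, so the rates are assumptions. Let a and p be the probabilities of at least one listed complaint in a 6-week period on modafinil and on placebo.

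- If complaints in the two periods overlap fully, the share meeting the trigger is max(a, p).
- If they are independent, the share is 1 − (1 − a)(1 − p).
- With 18 participants per sequence, the expected number meeting the trigger in period 1 is 18a + 18p.

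| a / p (assumed) | Share: overlap to independent | Of 36 | Of these, in period 1 |
|---|---|---|---|
| 10% / 5% | 10% to 14.5% | 3.6 to 5.2 | 2.7 |
| 20% / 10% | 20% to 28% | 7.2 to 10.1 | 5.4 |
| 30% / 20% | 30% to 44% | 10.8 to 15.8 | 9.0 |
| 40% / 30% | 40% to 58% | 14.4 to 20.9 | 12.6 |
| 50% / 30% | 50% to 65% | 18.0 to 23.4 | 14.4 |

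For example, at 20%/10% the independent share is 1 − 0.8 × 0.9 = 0.28, and 36 × 0.28 = 10.1.

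**4. From trigger to code break.** The number actually unblinded is the number meeting the trigger multiplied by the fraction of events that lead to a request. That fraction is not in the protocol. The counts above are therefore ceilings for each assumed pair of rates, reached only if every event leads to a request.

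**The case against.** The strongest reply is that unblinding happens only on request, so a sensible team would not open the code for a headache. This stands as a reason not to equate events with code breaks. It does not rescue the provision: the wording says unblinding will occur, the request has no criterion, and those entitled to make it include researchers who are meant to stay blinded.

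A second reply is that the article does not say the code reaches the participant or the outcome assessor, or that the researchers who may ask for it are the staff who assess. That is correct. Who receives the code and how breaks are logged may also be set out in the full protocol or in pharmacy procedures, so silence on those details is not the point. The point is the trigger that the article does state.

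Third, a participant whose drug is stopped may give no later on-treatment score. For that participant the problem is missing data rather than expectation. This also stands.

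A reader might infer more than the documents support:

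- That a large share of the trial will be unblinded. No event or request rate is given, and the Background describes the drug's side effects as limited.
- That both periods are lost for every participant unblinded. This can hold only for a break before the period 1 assessment.
- That the bias favours modafinil by some stated fraction of the 10-point target. No rates by treatment are given, and a participant unblinded because of an unpleasant effect need not rate the active drug better.

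**Conclusion.** The point holds as a contradiction in the text. The unblinding provision, combined with the adverse-event definition, allows the code to be opened for a minor complaint. It conflicts with the unqualified blinding of participants and non-pharmacy researchers, and it puts the blinding of assessors at risk. Its trigger is also wider than the drug-related wording used for discontinuation.

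The exposure matters because the primary outcome is self-reported, compared within participant, and each period's treatment reveals the other's. On the assumed rates, about 4 to 23 of 36 participants would meet the trigger, about 3 to 14 of them in period 1. These figures rest on the assumed complaint rates, on the range from full overlap to independence between periods, and on all participants completing both periods. Fewer would be unblinded if not every event leads to a request. The size and direction of any bias in the MFI-20 contrast cannot be determined from the protocol.

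**What to change.** Reconcile the unblinding sentence with the blinding statements under Consent and randomisation and under Assessments, so that:

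- a listed non-serious complaint does not by itself trigger a code break, and disclosure is limited to cases where the allocation must be known;
- emergency access through the pharmacy is kept;
- the code goes only to those who need it, so that outcome assessors, and where possible the participant, stay blinded;
- every code break is logged with its date and reason, including any among participants already enrolled.

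The unblinding trigger and the discontinuation wording under Patient population should be read against each other and the difference either explained or removed. No view is taken here on when study drug should be stopped.

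For the analysis, keep all participants in the primary model and report the number and timing of code breaks by treatment period. An analysis that leaves out scores recorded after a code break should be supportive only, with its selection risk stated, because it conditions on a post-randomisation event that may be related to treatment.

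The cost is an amendment to one passage, an instruction to the pharmacy and a log. It needs no extra participants or visits. Under Trial status, 24 of 36 participants had been enrolled, so the amended wording would protect the remaining 12 in full and the earlier ones only for scores still to be collected. Code breaks to date would have to be recovered from pharmacy records.

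### The serious-event wording merges seriousness with relatedness to modafinil, sets no limit by treatment period, and makes any event that leads to withdrawal serious

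*Protocol article*

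**What the plan says.** The serious-event wording is in the protocol article under Consent and randomisation: "A serious adverse events related to modafinil therapy can include developing a rash, or any event causing study participant withdrawal or hospitalisation while in the" (the final word is cut here; it makes the whole trial the window). The next sentence gives the ordinary category as a closed list of symptoms: "An adverse event will be defined as the occurrence of headache, nausea, anxiety/nervousness, insomnia, and diarrhoea".

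The same section ties breaking the blind to both categories: "Unblinding will occur in the event of an adverse or serious adverse event and will be performed by the pharmacy at the request of the" (the sentence ends by naming the trial's researchers and clinicians).

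The only other causality wording is under Patient population: "Study drug will be discontinued if there are any adverse events due to the drug (i.e. rash"). That section does not say how attribution to the drug is judged.

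The Therapy section fixes the crossover: "participants who initially received modafinil will be given a placebo or those who were given placebo will receive modafinil". No other definition of seriousness or relatedness appears in the article.

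**The concern.** A safety report normally keeps three questions apart: how serious the event was, whether the study drug caused it, and whether the participant left the trial. The quoted sentence answers all three at once. Relatedness is part of the defined term, withdrawal counts as a mark of seriousness, and the time window covers placebo and washout as well as modafinil.

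In a double-blind crossover every completer takes both treatments, so a label that presumes relatedness to one of them carries no information about which was being taken. If the safety report used the label as written, it would overstate serious modafinil-related events. It would also present dropouts over minor symptoms as serious toxicity. The article states that there is no Data Safety Monitoring Board, so the trial team's own classification carries more weight.

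**Working it through.** The article states no figure for this point, so there is nothing to reproduce. The check has two parts: applying the wording to example events, and measuring how much of the study window is off modafinil.

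**1. Applying the wording.** Two readings are possible. On the literal reading, every event that causes withdrawal or hospitalisation is serious and modafinil-related. On the favourable reading, relatedness is judged first, and the sentence then says which related events are serious.

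| Example event | Literal reading | Favourable reading |
|---|---|---|
| Hospital admission for an unrelated cause, placebo period | Serious, related | Not a related event |
| Headache in washout, participant leaves | Serious, related | Serious if judged related |
| Headache in modafinil period, participant stays | Adverse event, not serious | Adverse event, not serious |
| Same headache in modafinil period, participant leaves | Serious, related | Serious if judged related |

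The first row shows that the two readings give different counts of related serious events. The last two rows show that the withdrawal problem does not depend on the reading: the same headache changes class only because the participant left.

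**2. Share of the window off modafinil.** All inputs come from the Therapy section:

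- First period, 6 weeks: "All participants will be provided with 6 weeks’ worth of study drug after randomisation".
- Washout, 1 week: "After the study drug has been returned, participants will have a 1-week washout period".
- Second period, 6 weeks: "Lastly, after 6 weeks on the second round of the study drug, participants will be asked to return to the study centre".

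Time in study for a completer = 6 + 1 + 6 = 13 weeks, in either sequence.

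- On modafinil: 6/13 = 46%.
- On placebo: 6/13 = 46%.
- In washout: 1/13 = 8%.
- Off modafinil: (6 + 1)/13 = 7/13 = 54%.

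This is a share of calendar time. It becomes a share of events only if background withdrawals and hospitalisations arise at a constant rate unrelated to treatment, which is an assumption.

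Early departures change the share little, given 1:1 randomisation. If follow-up ended in the first period, half the time would be off modafinil (50%). If everyone stopped at the end of washout, it would be (3 + 1)/7 = 57%. The share therefore runs from 50% to 57%, with 54% for completers.

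**The case against.** The strongest reply is that the sentence is only loosely drafted. It says what such events can include, which is permissive, and it can be read with relatedness judged first. The article gives no rule for counting, attributing or tabulating events, and no planned analysis uses a related-event count. A condensed article may also leave causality assessment and event forms to the full protocol.

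Much of this stands, and it rules out four stronger conclusions that a reader might infer:

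- **That placebo and washout events are counted as modafinil toxicity.** The wording allows that label, but no counting rule is stated.
- **That modafinil and placebo can no longer be compared for serious harm.** The pharmacy allocates treatment from the randomisation schedule and can unblind after an event. Treatment at onset is recoverable whatever the label says.
- **That the two sections contradict each other on rash.** Patient population gives it as an event due to the drug, and Consent and randomisation gives it as a related serious event. These agree.
- **That the reported proportion shifts by some number of percentage points.** The article gives no event rates, so any assumed count of misclassified events would have no source.

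The reply does not remove the fault. The article did not leave the definition out: it printed one that supports two readings with different related-event counts. Even the favourable reading keeps withdrawal as a mark of seriousness.

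**Conclusion.** The point holds as a defect in a stated definition. The sentence runs seriousness and relatedness together, has no limit by treatment period, and makes a mild event serious when it leads to withdrawal. Nothing else in the article corrects it.

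The exposure is a window that is 54% off modafinil for a completer. That figure describes the schedule. Treating it as the share of background events that begin off modafinil rests on the constant-rate assumption, and the number of such events cannot be estimated from the article.

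The effect is confined to safety reporting. The change is worth making because it is cheap and removes an avoidable distortion from the safety results.

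**What to change.** Reword the definition and adjust the event form:

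1. Define seriousness by the outcome of the event alone.
2. Remove withdrawal from the serious criteria, and report withdrawals separately with their reasons.
3. Take relatedness to modafinil out of the definition. Record it for each event as a separate judgement made before any unblinding. The order matters because the article ties unblinding to the occurrence of an event.
4. Tabulate events by treatment at onset, with washout shown separately.
5. Reconcile the wording on events due to the drug (Patient population) with that on events related to modafinil (Consent and randomisation), so that both rest on one stated meaning. This does not prescribe when study drug is stopped.

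The cost is a small change to the protocol wording and the event form. The reported number of related serious events may change. Trial status gives 24 of 36 participants enrolled at the time of writing, so earlier events would need re-tabulating by onset date, assuming those dates were recorded. Any event already unblinded should be marked, because its relatedness can no longer be judged blind.

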### Sample size

The study was designed to have 80 % power in detecting a 10 point decrease in self-reported fatigue on the MFI after 6 weeks of modafinil treatment with a type I error rate of 0.05 and assuming standard deviation in the patient population of 14. Using previously reported effects of modafinil on fatigue for stroke survivors [10], multiple sclerosis [12] and a Cochrane review [13] a total sample size of 34 is required for a crossover study. Assuming modest participant dropout and study drug compliance, we aim to recruit 36 participants in total. The crossover design reduces the number of participants required and the negative effects of missing data given the small number of dropouts expected [14].

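### The adverse-event definition is a closed list of five complaints, so unlisted events that lead to neither withdrawal nor hospitalisation fall outside both safety definitions

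*Protocol article*

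**What the plan says.** The protocol article uses the term adverse event in two sections.

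- **Consent and randomisation** defines it: "An adverse event will be defined as the occurrence of headache, nausea, anxiety/nervousness, insomnia, and diarrhoea". The preceding sentence says that a serious adverse event related to modafinil "can include developing a rash, or any event causing study participant withdrawal or hospitalisation while in the study". The same paragraph makes a consequence depend on these terms: "Unblinding will occur in the event of an adverse or serious adverse event".
- **Patient population**, after the exclusion criteria, makes a second consequence depend on the term: "Study drug will be discontinued if there are any adverse events due to the drug (i.e. rash".

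Three other sections give context. The Assessments section describes the scheduled visits, beginning "The assessment at each time point will include the MFI-20, the Montreal Cognitive Assessment (MoCA), the Fatigue Severity Scale (FSS" and continuing with the mood and quality-of-life scales; it names no adverse-event enquiry. The sections on primary outcomes, secondary outcomes and statistical analysis name no safety outcome and no safety comparison. The opening of Methods/design says that "no Data Safety Monitoring Board will be required".

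**The concern.** A list limited to complaints named in advance records what is already expected. An event that is not on it is counted only if it is bad enough to end participation or put the person in hospital. The events lost lie between those two categories: unlisted, not leading to withdrawal or admission, but possibly relevant to whether people with long-standing post-stroke fatigue can tolerate the drug. At stake is the completeness of whatever adverse-event table the trial reports. The efficacy analysis is not affected.

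The second difficulty is that the term has two meanings. One section treats rash as the example of an adverse event. The other leaves rash off the adverse-event list and places it only among serious events, with no condition on severity. Two actions, unblinding and stopping study drug, depend on a term whose scope the article does not settle.

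**Working it through.** No stated figure is in dispute, so the check is a reading of the two definitions followed by an illustration of scale.

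**Step 1. Is the list closed?** The adverse-event sentence is worded as a definition and contains no phrase that would make the five complaints examples. The serious-event sentence just before it is open in form. The contrast within one paragraph favours reading the list literally. No other section shown supplies a broader definition.

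**Step 2. Which events meet which definition?**

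| Event | On the five-item list? | In the serious category? | Counted? |
|---|---|---|---|
| Headache, nausea, anxiety/nervousness, insomnia, diarrhoea | Yes | Only if it leads to withdrawal or hospitalisation | Yes |
| Rash | No | Yes, named | Yes |
| Unlisted event leading to withdrawal or hospitalisation | No | Yes | Yes |
| Unlisted event leading to neither (palpitations, dizziness, fall without admission) | No | Not named or described there | No |

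Only the last row is lost.

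**Step 3. Do the two sections agree?** The patient-population section speaks of "any adverse events due to the drug (i.e. rash", so rash is an adverse event there. Read literally, the definition in the consent section does not make it one. Rash is still counted under either section, so the disagreement concerns its class and not whether it is recorded.

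**Step 4. Scale, as illustration only.** The input from the article is its Sample size section: "we aim to recruit 36 participants in total". The event rate p is an assumption; the article gives none. Suppose all 36 are exposed and the event is unlisted and never leads to withdrawal or hospitalisation. The expected number of affected participants omitted is 36p, and the chance that at least one is omitted is 1 − (1 − p)^36.

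| Assumed p | 36p | 1 − (1 − p)^36 |
|---|---|---|
| 2% | 0.7 | 52% |
| 5% | 1.8 | 84% |
| 10% | 3.6 | 98% |
| 20% | 7.2 | over 99.9% |

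These figures show how many people a given rate would mean in a trial of this size. They are not evidence that such an event occurs, and dropout before the modafinil period would lower them.

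**The case against.** The strongest reply is that this is a journal article. The full protocol (version 3) is not shown and may record events more broadly. The sentence also closely follows the unblinding rule and may have been meant to say what prompts unblinding, not what is recorded. Both are possible. But the article is not silent here: it states a definition, and nothing shown widens it or limits it to unblinding. How and when events are asked about could well be left to the full protocol, and that omission is not the point made here.

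On rash, it can be said that serious events are ordinarily a subset of adverse events, so both sections can hold. That is fair as to whether rash is counted. It does not remove the mismatch with a definition that, as written, leaves rash out.

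A reader might infer several stronger conclusions that the documents do not support:

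- *The trial cannot detect any unexpected harm.* The serious category is open and covers any event leading to withdrawal or hospitalisation, expected or not.
- *Recorded events are the only safety evidence, and mood change would be missed.* Mood (DASS 42), cognition (MoCA) and quality of life (SSQoL) are measured at every assessment, and anxiety/nervousness is on the list.
- *Counting by presumed drug relation distorts the comparison of modafinil with placebo.* The five-complaint definition has no relatedness condition; only the serious-event sentence mentions relation to modafinil. The article plans no formal safety comparison.
- *Relatedness must be judged blind.* The same paragraph provides for unblinding when an event occurs.
- *The absence of a monitoring board makes the gap worse.* A board would see only what is recorded, so this is context and not part of the defect.
- *Stroke survivors are a new population for the drug.* The Background cites case reports and an earlier study in stroke.

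The last objection bears on the remedy. Because unblinding and discontinuation are both tied to the term, widening the definition alone could extend both to minor events, in a trial whose primary outcome is self-reported. That objection stands, and the fix has to deal with it.

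**Conclusion.** The point holds in a limited form. Under the definitions as written, an unlisted event that leads to neither withdrawal nor hospitalisation is neither an adverse event nor within the description of serious events, and an adverse-event tabulation built on them would be incomplete. The two sections also use the term differently, with rash as the visible case.

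The size of the gap cannot be taken from the documents. For assumed rates of 2% to 20%, between about 0.7 and 7.2 of 36 participants would go uncounted for each such event. The conclusion rests on a literal reading of the definition and on the full protocol not widening it. It is a defect in safety recording that should be corrected; it does not affect the sample size or the efficacy model.

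**What to change.** For recording and reporting:

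1. Define an adverse event as any untoward medical occurrence after the first dose, regardless of presumed cause.
2. Keep the five complaints as solicited events within that definition, and capture all others through one open question at the existing visits.
3. Define serious events without reference to relatedness, and record presumed relation to the drug as a separate item.
4. Classify rash once, and make the patient-population and consent sections agree on it.
5. Tabulate events by treatment period.

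At the same time, reconcile the statements on unblinding and on discontinuation with the new recording definition, so that broader recording does not automatically widen either trigger. Which events should prompt either action is a clinical decision for the sponsor and investigators, and no rule is proposed here.

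The cost is revised wording in two sections, one question on the visit form and slightly more recording work, with no extra visits. If the full protocol already has a broader definition, it is enough to say so and align the published text. The Trial status section reports 24 of 36 participants enrolled, which leaves 36 − 24 = 12 to enrol, so event capture would differ between participants before and after the change. The report should state the date of the change and note that difference.
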